#### Blinding

A team of psychiatric nurses at the clinic will be trained to conduct patient assessments before, during, and after treatment. Assessors will be aware of the patient’s treatment allocation. Genuine blinding of assessors is not feasible given the technical devices that need to be displayed in the project. Thus, blinding will not be possible at the patient or therapist level. At the analysis stage, however, the participants’ identity will not be known to the researcher; that is, all data will be available according to group allocation (1, 2, or 3).

### Procedure

Recruitment will be done at Riddargatan 1, where people starting a treatment program for alcohol dependence will be informed about the study by the physician in charge. Patients expressing willingness to participate will be included. Information about the devices under study and the study procedures is provided by the counselor in charge of the treatment at the first treatment session, after assessing inclusion and exclusion criteria. Recruitment will also occur through advertisements placed in the waiting room.

To improve adherence, data on participant use of the devices will be continuously monitored. If necessary, the study coordinator will send reminders via text messages to the participants. Also, the devices will generate reminders (e.g., “push notifications”) for the participants.

When participants are included in the study they will be given timings for follow-up meetings at 3 and 6 months after study baseline. The follow-up visits will be with the study coordinator. All study questionnaires will be stored in a Case Record Form (CRF). Between the study visits, all CRFs will be kept in a locked and secure data archive room.

The counselors involved in this study are all certified therapists, with relevant specialist training for the treatment programs chosen for this study; that is, pharmacological treatment combined with the “Guide to better drinking habits” or the “Guide to Controlled drinking”, both based on cognitive behavioral treatment. Medications that will be used in this study are naltrexone and acamprosate.

The project is planned to start in 2018. Participant recruitment is expected to be completed by the end of 2019. Follow-ups will be completed by July 2020. Results will be reported during the fall of 2020.

### Baseline and follow-up assessments

Baseline data for this study, the TLFB interview, the AUDIT questionnaire, and the biomarker PEth, as well as diagnostic instruments for the diagnosis of alcohol dependence are collected routinely at intake for all patients at Riddargatan 1.

#### RCT outcome measures

##### Primary outcome measure

The primary outcome is the number of days with heavy drinking, defined as four or more standard drinks (12 g alcohol/drink), measured by the timeline follow back instrument (TLFB) and AUDIT.

##### Secondary outcome measures

The secondary outcomes are weekly alcohol consumption, measured by TLFB and AUDIT, and PEth values in blood at 3-month and 6-month follow-up, and the number of days with BAC levels exceeding 60 mg/100 ml.

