**Methods:**

The study is a three-armed RCT with follow-ups 3 and 6 months after randomization. In total, 375 adults (age 18+ years) diagnosed with alcohol use disorder (AUD) will be invited to participate in a 3-month intervention. The primary outcome is the number of days with heavy drinking, defined as four or more standard drinks (12 g alcohol/drink) and measured by the timeline follow back (TLFB) and Alcohol Use Disorder Identification Test (AUDIT) instruments at 3-month and 6-month follow-up. Secondary outcome measures include weekly alcohol consumption, measured by the TLFB, AUDIT, and phosphatidylethanol in blood values at 3-month and 6-month follow-up (number of days with blood alcohol concentration levels exceeding 60 mg/100 ml).

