In this project we aim to examine two mobile phone applications (apps), “Glasklart” and the combination of a portable breathalyzer with a mobile phone application “iBAC”, in the treatment of AUD. The Glasklart app enables the user to make instant, continuous, and anonymous registration of the alcohol volume (i.e. standard drinks) consumed on each occasion, with the possibility to also share information with a caregiver. The advantages of using a smartphone app are several; smartphones may store and share data in real time, give geographical location, allow for on-demand communication, are almost always on, and are portable [21]. The iBAC device gives a biologic measure of the current blood alcohol concentration (BAC). The advantage is that this provides an estimate that is independent of self-report and that this device is also easily managed using a mobile phone. In general, alcohol consumption data are collected in retrospect, thus increasing the risk of recall bias [22]. Possible consequences of incorrect information regarding alcohol consumption are several; for example, difficulties in clinically assessing alcohol-related problems and evaluating treatment of alcohol-related problems for the individual, and difficulties in examining the health effects of alcohol consumption. This project enables *instant* assessment of alcohol consumption which in turn may allow for more accurate reports.

We will conduct a randomized controlled trial (RCT) to examine the effects of using apps as complements to standard treatment on alcohol consumption in adults with AUD. A comparison group will receive standard treatment only, described later. Specifically, we aim to validate Glasklart and iBAC as instruments for assessing alcohol consumption, and to investigate whether assessment (self-monitoring), using Glasklart or iBAC, has a reducing effect on alcohol consumption.

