#### Randomization

Following the first treatment session, the counselor informs the study coordinator about the new study participant (see Fig 2 for participation flow diagram). The coordinator records baseline data in a study database and initiates the randomization procedure. This procedure is conducted by an administrator with no other role in this study. Randomization is done by a computer program, where participants are randomized (in blocks of 10) either to treatment as usual (TAU), or TAU + Glasklart, or TAU + iBAC. TAU in this study at Riddargatan 1 involves pharmacotherapy in combination with manualized psychological treatment—either the “Guide to better drinking habits”, building on theories on guided self-change [23–25], or the “Guide to Controlled drinking”, referring to theories on behavioral self-control training [26]. Each study participant is given a study number (1–375). Only the administrator has access to the code key, where the study number is coupled with the participant’s person number. The code key is stored in a locked cabinet in the patient archive at the clinic.

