**Fig. 2 Fig2:**
[figure not shown]
Participant flow diagram. AUD alcohol use disorder, AUDIT Alcohol Use Disorder Identification Test, ICD 10 International Statistical Classification of Diseases and Related Health Problems 10th revision, ITT intention to treat, TAU treatment as usual, TLFB timeline follow back

At the second treatment session, the counselor collects the signed informed consent document. The counselors then explain and demonstrate the two devices: Glasklart and iBAC. Each patient randomized to the iBAC intervention is provided with an iBAC breathalyzer (one of the smallest breathalyzers available) for the duration of the study. The apps (Glasklart and iBAC respectively) will be installed on the participants’ smartphones. The iBAC breathalyzer is linked to the mobile phone via Bluetooth and the information on the BAC level is saved in the breathalyzer and mobile app. The user identifies herself or himself using a color-coding photographic function to verify that the intended user takes the test.

Patients randomized to Glasklart will be instructed to register every glass of alcohol they drink in the Glasklart app. They will receive automatic reminders, a so-called push notification that pops up on the mobile device after half an hour (after first registration), to continue registration if they have consumed more alcohol (i.e., “do you have anything more to register?”). Patients randomized to iBAC treatment will also receive a message on their mobile phone instructing them to use their iBAC breathalyzer at hourly intervals during drinking occasions, as long as these go on. That is, the iBAC is programmed to contact the patient with push notification according to a preset time schedule. The patients can then review their drinking through the apps respectively. Glasklart will describe the number of drinks consumed, when and where, in what mood, and whether alone or together with others. iBAC will describe the BAC level at different time points. Both of these devices can be viewed on a daily, weekly, or monthly basis. Moreover, the information collected is also visible for the counselors.

At all sessions of the treatment program, at baseline, at 3 months, and at a follow-up after 6 months, the timeline follow back (TLFB) and AUDIT will be recorded, and blood tests will be analyzed for phosphatidylethanol in blood (PEth).

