### Statistical analyses and power calculation

The sample size has been estimated from the primary outcome variable, heavy drinking days during the past 30 days before baseline, at 3 months and at 6 months after baseline. Based on the assumption that the effect size of the intervention will be in the range of 0.4 SD in groupwise comparisons (alpha 5% and two-tailed tests) we need at least 98 individuals in each of the three treatment arms, and given an expected 25% dropout rate this motivates our choice of *N* = 375.

Data will be analyzed according to intention to treat (ITT). A secondary analysis will be per protocol for those participants who have contributed data at baseline and at 3-month follow-up. Primary and secondary outcome measures will be analyzed through ANOVA for repeated measures, with time (baseline, 3 months, and 6 months) as the dependent variable and type of intervention (TAU, or TAU + Glasklart, or TAU+ iBAC) as the independent variable.

A multiple regression analysis will be performed to investigate the extent to which the different predictor variables (consumption level and pattern, severity of dependence) contribute to the variation in the primary and secondary outcome measures.

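### Days with BAC above 60 mg/100 ml cannot be compared between arms or with baseline as planned: the only BAC device described goes to one arm, after randomization

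*Protocol article*

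**What the plan says.** The Protocol article, under RCT outcome measures (Secondary outcome measures), names weekly consumption, PEth and "the number of days with BAC levels exceeding 60 mg/100 ml". No instrument is attached to the last of these.

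Statistical analyses and power calculation states: "Primary and secondary outcome measures will be analyzed through ANOVA for repeated measures". The time points are baseline, 3 months and 6 months, and the groups are TAU, TAU + Glasklart and TAU + iBAC. No secondary outcome is exempted.

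On measurement, the Background says: "The iBAC device gives a biologic measure of the current blood alcohol concentration (BAC"). The text below Fig. 2 says who gets the device: "Each patient randomized to the iBAC intervention is provided with an iBAC breathalyzer". On timing, the Randomization section places baseline recording and allocation after the first treatment session: "The coordinator records baseline data in a study database and initiates the randomization procedure". The devices come at the second session: "The counselors then explain and demonstrate the two devices: Glasklart and iBAC".

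The abstract words the outcome differently. There, "number of days with blood alcohol concentration levels exceeding 60 mg/100 ml" stands in brackets directly after the PEth values at 3 and 6 months, as if it explained them.

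**The concern.** Three statements do not fit together: the outcome belongs to the randomized comparison, the means of measuring it exists in one arm only, and the analysis needs it in three arms at three times.

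At stake is a declared RCT outcome that cannot answer the treatment question. When the data arrive, the analyst will either have to drop it unannounced or improvise a substitute definition, possibly with the other results already known. The abstract makes this harder to settle, because it leaves open whether BAC days are a separate outcome or a gloss on PEth.

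**Working it through.** The outcome has no planning figure of its own. The article's only sample size figure, at least 98 per arm for the primary outcome, is consistent with its inputs. For 0.4 SD, two-sided alpha 5% and an assumed power of 80% (power is not stated), n = 2 × (1.96 + 0.8416)² / 0.4² = 98.1, which rounds up to 99. This is context only, since no sample size fills a cell in which nothing is measured.

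**Step 1: sources of BAC named in the article.**
- *iBAC breathalyzer*: BAC at different time points, in the iBAC arm only (text below Fig. 2).
- *Glasklart*: number of drinks, time, place, mood and company; no BAC (same place).
- *TLFB*: interview on consumption over the last 30 days, all arms; no BAC (Instruments).
- *AUDIT*: questionnaire, all arms; no BAC.
- *PEth*: a blood value from a sample taken at a visit, all arms. It is not described as giving a daily BAC, and a single value is not a count of days above a threshold.
- *Baseline set*: TLFB, AUDIT, PEth and the diagnostic instruments (Baseline and follow-up assessments). BAC is not among them.

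**Step 2: timing.** Baseline is recorded and randomization started after session 1. The breathalyzer is introduced at session 2. No baseline BAC can exist, even in the iBAC arm.

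**Step 3: the cells that the planned analysis needs (3 arms × 3 times = 9).**

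| Arm | Baseline | 3 months | 6 months |
|---|---|---|---|
| TAU | none | none | none |
| TAU + Glasklart | none | none | none |
| TAU + iBAC | none | possible | possible |

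At most 2 of 9 cells (22%) can hold measured BAC.

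**Step 4: participants.** With equal arms, 375 / 3 = 125 per arm. Without a breathalyzer: 2 × 125 = 250 of 375 (67%). Without a baseline value: 375 of 375.

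**Step 5: what can be estimated.** A between-arm contrast needs values in at least two arms, and there is one. A change from baseline needs a baseline value, and there is none. Having data coincides exactly with being in the iBAC arm, so neither a mixed model nor imputation can recover the contrast from the data. What remains is a description of the iBAC arm at follow-up.

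**Step 6: could BAC be estimated instead?** TLFB drinks are collected in all arms and at baseline. The article gives no formula, however, and its listed demographics cover age, gender, occupation and marital status but not body weight. Drinking duration is not listed for all arms either. As written, no estimated BAC is specified.

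**The case against.** The strongest reply is that the outcome section names no source for BAC. That the outcome can be observed only with iBAC is an inference from iBAC being the sole BAC instrument described. TLFB is taken in every arm at all three times, the article condenses a fuller protocol, and deriving an outcome is often left to that document or to the SAP. This stands in part: the outcome is not impossible under every conceivable definition, and a reader who concludes that it is goes beyond the text. It does not remove the conflict. If measured BAC is meant, the stated analysis cannot be run, and no SAP can supply readings in arms without a device. If estimated BAC is meant, that is a different outcome. It would rest on self-report, whereas the Background gives independence from self-report as the advantage of the breathalyzer.

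A reader might also infer that untested days, or participants without a device, would be scored as zero days, so that the iBAC arm looks worse by construction and its least adherent users look best. The documents do not support this, because no scoring rule is stated and nobody proposes such an imputation. Nor do they give any figure for how often drinking days would be tested. The plan does provide hourly prompts, continuous monitoring of device use and text reminders. All that can be said is that the count depends on use of the device.

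The abstract point is mainly editorial. The outcome section, which is the operative text, separates PEth from BAC days.

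Finally, this is the last-listed secondary outcome. The primary outcome, weekly consumption and PEth are measured in all arms and at baseline, and the sample size does not depend on BAC. That limits the severity.

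**Conclusion.** The point holds. The stated outcome, the allocation of the device and the stated analysis contradict one another. Measured BAC can exist in at most 2 of 9 arm-by-time cells. About 250 of 375 participants have none, and no participant has a baseline value. Neither the difference between arms nor the change from baseline is estimable.

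This rests on two assumptions: that iBAC, the only BAC instrument described, is the intended source, and, for the figure of 250, that the arms are equal in size, since no allocation ratio is stated. The cell count and the empty baseline do not depend on the second assumption.

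This should be fixed, but it does not threaten the trial's main conclusion.

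**What to change.** Choose one of two repairs and state it before any between-arm results are seen.

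1. Remove BAC days from the between-arm secondary outcomes. Report them descriptively in the iBAC arm, or within the validation study, which already uses the iBAC readings. Give the number of days tested alongside, because the count depends on device use. The cost is wording in the protocol and the registry, and the loss of one outcome that could not have been compared.
2. If an estimated BAC is intended, rename and redefine the outcome. Give the formula, and derive it only from data collected identically in all arms and at baseline. The cost is extra data items for everyone from baseline on, and an outcome that relies on self-report.

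Either way, keep PEth as the biological between-arm secondary outcome, and in the abstract separate it from the BAC phrase so that the two no longer read as one measure.

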#### Validation study

The validation study will correlate registered consumption in the Glasklart app and iBAC respectively, with results from the TLFB, AUDIT, and PEth. Agreement will also be tested using the intra-class correlation (ICC) and kappa coefficient statistics, for consumption structured as groups.

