### Key research questions

Do mobile phone applications provide better (i.e., higher) estimates of alcohol consumption than current measurement methods?Does the use of these devices, on the one hand featuring self-monitoring of alcohol consumption, and on the other measuring blood alcohol levels through a breathalyzer connected to a mobile phone, have an effect on the user’s alcohol consumption?How are Glasklart and iBAC perceived by the users? This question includes assessments of the technical components, such as app features including reminders, geolocalization, and registration of mood (qualitative study).

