#### Instruments

Demographics: age, gender, occupation, and marital status (baseline only).Timeline follow back: structured interview for assessment of alcohol consumption during the last 30 days [27].Alcohol Use Disorder Identification Test (AUDIT) questionnaire [28], modified to the 3-month reference period in the follow-up.Severity of alcohol dependence is measured by the number of fulfilled diagnostic criteria for the diagnosis alcohol dependence, according to ICD-10.Short Alcohol Dependence Data (SADD) [29, 30]: this instrument is currently undergoing Swedish validation and will be published during 2018.Client Satisfaction Questionnaire (CSQ) [31].The Hospital Anxiety Depression Scale (HAD) [32]: 14 items scored 0–3 based on how the respondent felt during the past week.The Short Form Health Survey (SF-12) [33]: 12 items assess functional health and wellbeing from the respondent’s perspective.Phosphatidylethanol (PEth): blood samples will be collected by staff at Karolinska Universitetssjukhusets Laboratorium (KS Lab) in Stockholm and will be analyzed at KemLab/LS Laboratorium. The results will be delivered through the electronic patient record system (Take Care) within 2–3 days. The results will be printed and anonymized by the study coordinator and then placed in the CRF.

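### Research question 1 asks whether the apps record more drinking than current methods, but correlation, ICC and kappa cannot show the direction or size of a difference

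*Protocol article*

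**What the plan says.** Under Key research questions, the protocol article asks: "Do mobile phone applications provide better (i.e., higher) estimates of alcohol consumption than current measurement methods". The parenthesis makes this a directional question about the level one method records against another. The Background adds a broader aim: "we aim to validate Glasklart and iBAC as instruments for assessing alcohol consumption".

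The section Validation study gives the only analysis for this part of the project: "The validation study will correlate registered consumption in the Glasklart app and iBAC respectively, with results from the TLFB, AUDIT, and PEth". It continues: "Agreement will also be tested using the intra-class correlation (ICC) and kappa coefficient statistics, for consumption structured as groups". The section on statistical analyses and power deals with the trial outcomes by arm. It contains no within-person comparison of an app with the TLFB.

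The measures are described in the text after Fig. 2 and under Instruments. For the first app, "Glasklart will describe the number of drinks consumed, when and where, in what mood, and whether alone or together with others". For the breathalyzer, "iBAC will describe the BAC level at different time points". The TLFB is a "structured interview for assessment of alcohol consumption during the last 30 days". AUDIT at follow-up refers to three months, and PEth is a blood marker.

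**The concern.** The question and the analysis do not match. Whether the app reads higher calls for a signed difference between two measurements on the same person. Correlation measures how closely two measurements move together and ignores a constant shift. Agreement coefficients can fall when there is a systematic difference, but they mix it with random disagreement and do not carry its sign.

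Reported exactly as described, the validation study could yield a full table of coefficients and still not say whether participants register more or less drinking in Glasklart than they report in the TLFB. The first key research question would then go unanswered although the data to answer it are in hand. The article names both the question and the statistics, so this is a mismatch in what is written and not a detail left for a later document.

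**Working it through.** **Plan's own figure.** The article gives no sample size or precision for the validation study. Its only such figure is 98 per arm for the randomized comparison (0.4 SD, two-sided 5%). With 80% power, which the article does not state, 2 x (1.96 + 0.842)^2 / 0.4^2 = 98.1, so that figure is reproduced. This point does not depend on it.

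**Does each planned statistic respond to direction?** Two bivariate-normal measures were simulated (200,000 pairs, assumed correlation 0.8), and the app was shifted by a constant.

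| Statistic | App 0.5 SD lower | No shift | App 0.5 SD higher |
|---|---|---|---|
| Pearson r | 0.80 | 0.80 | 0.80 |
| ICC, consistency | 0.80 | 0.80 | 0.80 |
| ICC, absolute agreement | 0.71 | 0.80 | 0.71 |
| Kappa, four groups, unweighted | 0.30 | 0.39 | 0.30 |
| Mean paired difference (SD) | -0.50 | 0.00 | +0.50 |

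The 0.71 also follows directly. With equal variances of 1, absolute-agreement ICC = correlation / (1 + shift^2 / 2) = 0.8 / (1 + 0.25 / 2) = 0.71. The shift enters as a square, so its sign is lost.

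**A proportional difference.** Suppose the app records exactly twice, or exactly half, the TLFB amount. Pearson r is 1.0 in both cases. Absolute-agreement ICC is 4 / (5 + 1/CV^2), where CV is the coefficient of variation of consumption. For an assumed CV of 0.5 this is 4/9 = 0.44, and for a CV of 1 it is 4/6 = 0.67. The values are the same for doubling and halving, so the discrepancy would be noticed but not its direction.

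**Which pairs allow a level comparison?** There are 2 devices x 3 comparators = 6 pairs. Only Glasklart with TLFB is naturally the same quantity, an amount of alcohol consumed. iBAC yields concentrations at time points, AUDIT a questionnaire result over another window, and PEth a blood value.

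**Precision of the signed comparison.**
- Users per arm: 375 / 3 = 125. With the article's 25% dropout, 125 x 0.75 = 93.75, about 94. That all of them have usable app records is an assumption.
- 95% CI half-width: 1.96 / sqrt(94) = 0.20 SD of the differences.
- Detectable with 80% power (assumed): (1.96 + 0.842) / sqrt(94) = 0.29 SD of the differences.
- If only half had usable records (n = 47, for illustration): 1.96 / sqrt(47) = 0.29.
- In SD of the measure itself, the half-width is 1.96 x sqrt(2(1 - correlation) / n). For n = 94 this is 0.20 at a correlation of 0.5 and 0.13 at 0.8, both assumed.

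**A formal test of which method tracks PEth better.** Assume PEth correlations of 0.60 and 0.50, an app-TLFB correlation of 0.5 to 0.8, and n = 94. A test for dependent correlations then has about 23% to 46% power.

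**The case against.** The strongest defence is that the Background also states a general validation aim, which correlation, ICC and kappa do serve, and that a two-sentence account in an article leaves limits of agreement, exact windows and the type of ICC to a fuller document. Absolute-agreement ICC and kappa are not blind to a systematic difference, and the cross-table behind kappa would show which method reads higher. All of this is fair. However, the article does not promise to report that table, and none of the statistics it names carries a sign. The directional question remains without an analysis.

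Three stronger readings are tempting, and the documents do not support them.

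- *That ICC will be run across incompatible units.* The sentence on agreement ends by confining it to consumption put into groups. It does not say that ICC will be applied to raw BAC, AUDIT totals or PEth values, and cut-points for common categories may stand elsewhere. Unlike units are no fault in a correlation.
- *That PEth is ignored as an independent anchor.* Both devices are already to be correlated with it. What is not stated is a comparison of the app-PEth with the TLFB-PEth correlation.
- *That the TLFB will be filled in from the app, inflating agreement.* Patients and counselors can see the app records, so the risk exists. But the TLFB is a structured interview, the follow-up visits are with the study coordinator, and nothing says that app records are consulted.

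Nor does the r = 1.0 example by itself show that the plan would miss a doubling, since absolute-agreement ICC would fall well below 1.

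**Conclusion.** The concern holds in a limited form: the stated validation analysis cannot answer research question 1 as the article poses it. Correlation and consistency ICC are unaffected by a constant shift. Absolute-agreement ICC and kappa fall equally in both directions (0.80 to 0.71 and 0.39 to 0.30 for half an SD, given an assumed correlation of 0.8). Only the size of these falls depends on the assumed correlation and group cut-points; the loss of sign in r and ICC does not.

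A signed comparison is feasible with planned data. Its half-width is about 0.20 SD of the differences if about 94 Glasklart users have usable records, and wider if app use is incomplete. The change should be made, but it touches a secondary part of the project. The randomized comparison and its primary outcome are unaffected.

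**What to change.** 1. Name as the main analysis for question 1 the within-person difference, Glasklart minus TLFB, in standard drinks and in heavy drinking days. Take both from the same 30-day TLFB window, for example the one before the 3-month visit. Report the mean difference with a 95% CI and Bland-Altman limits of agreement, and the number of participants with usable app records.
2. Keep correlation for iBAC, AUDIT and PEth. Use ICC only where both measures express the same quantity on a common scale. State that question 1, as a question of level, is then answered for Glasklart.
3. A higher estimate is not by itself a better one, so report the app-PEth and TLFB-PEth correlations side by side as supportive evidence. A formal test of their difference should not be relied on, given its limited power at about 94 per arm.

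The cost is a few lines in the protocol or analysis plan and a little extra analysis. No new data, visits or participants are needed.

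### No validation statistic named in the article gives the direction of the app-versus-TLFB difference, so the named analyses do not answer the first research question (are app estimates higher?)

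*Protocol article*

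**What the plan says.** Under Key research questions, the first question is "Do mobile phone applications provide better (i.e., higher) estimates of alcohol consumption than current measurement methods". The Background gives the matching aim: "we aim to validate Glasklart and iBAC as instruments for assessing alcohol consumption".

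The Validation study section is the only part that sets device readings against the other instruments. It names three statistics. The first is correlation: "The validation study will correlate registered consumption in the Glasklart app and iBAC respectively, with results from the TLFB, AUDIT, and PEth". The other two are agreement coefficients: "Agreement will also be tested using the intra-class correlation (ICC) and kappa coefficient statistics, for consumption structured as groups". The form of the ICC and the weighting of kappa are not given.

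The section Statistical analyses and power calculation adds two analyses. One is for the trial outcomes: "Primary and secondary outcome measures will be analyzed through ANOVA for repeated measures", with arm as the factor. The other concerns predictors of outcome: "A multiple regression analysis will be performed to investigate the extent to which the different predictor variables". No section names a within-person difference, a ratio or a signed test of app against TLFB.

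**The concern.** Whether one method gives higher values than another in the same people is a question about a paired difference, which has a sign and a unit. Correlation, ICC and kappa have neither. The validation study could report a high correlation and a moderate kappa and still not say whether the app captured more, less or the same drinking as the TLFB. The article treats a higher estimate as a better one, so direction is what the question turns on. This point takes that equation as written and does not dispute it.

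**Working it through.** The article gives no figure for the validation study, so there is none to reproduce. The check asks what each named statistic can show.

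**Step 1: an argument that needs no assumed values.** Correlation, ICC and kappa (unweighted, or with symmetric weights) do not change if the two methods swap labels. Take any data set in which the app reads higher than the TLFB and swap the columns. The app now reads lower, and every coefficient is the same. The value of the coefficient therefore cannot tell which method is higher.

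**Step 2: size under one set of assumptions.** These values are assumed, not from the article: true 30-day consumption with mean 20 and SD 8 drinks, error SD 3 in each method, the app shifted by a constant *s*, and kappa groups cut at 10, 20 and 30. With these:

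- Correlation and consistency ICC: 8² / (8² + 3²) = 64/73 = 0.877 for every *s*.
- Absolute-agreement ICC: 64 / (73 + *s*²/2). The shift enters only as a square. For *s* = −4 or +4 this is 64/81 = 0.790; for −6 or +6 it is 64/91 = 0.703.

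A simulation of 200,000 pairs agrees:

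| Shift *s* | Pearson | ICC, consistency | ICC, absolute | Kappa, unweighted | Kappa, weighted | Mean app − TLFB |
|---|---|---|---|---|---|---|
| −6 | 0.877 | 0.877 | 0.704 | 0.232 | 0.622 | −5.99 |
| −4 | 0.877 | 0.877 | 0.791 | 0.378 | 0.701 | −3.99 |
| 0 | 0.877 | 0.877 | 0.877 | 0.539 | 0.781 | 0.01 |
| +4 | 0.877 | 0.877 | 0.790 | 0.379 | 0.701 | 4.01 |
| +6 | 0.877 | 0.877 | 0.702 | 0.232 | 0.621 | 6.01 |

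Only the last column, which the article does not name, recovers the sign and the size.

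**Step 3: a fall in agreement does not measure bias.** Keep the shift at zero and raise the app's error SD from 3 to 5. The mean error variance is (9 + 25)/2 = 17, and the absolute-agreement ICC is 64/(64 + 17) = 0.790. That equals the value for a shift of 4 drinks.

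**Step 4: a proportional bias on skewed data.** Assume log SD 0.8 and a log error SD of 0.2 in each method. Consistency ICC on the log scale is 0.64/0.68 = 0.941 whatever the multiplier. For a multiplier of 1.3 or 1/1.3 the log shift is ±0.262, and half its square is 0.0344. Absolute-agreement ICC is then 0.64/(0.68 + 0.0344) = 0.896 in both cases.

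**Step 5: can the other analyses supply the direction?** The repeated-measures ANOVA compares arms on the trial outcomes, and the regression relates predictors to those outcomes. Neither sets a person's app record against the same person's TLFB.

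**Step 6: precision of a paired difference.** The planned 375 participants in three arms give 125 per arm. After the stated 25% dropout, 125 × 0.75 = 93.75, about 94. With one pair per person, the 95% CI half-width is t(0.975; 93)/√94 = 1.986/9.695 = 0.20 SD of the differences.

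**The case against.** The strongest reply is that the Validation study section is a two-sentence summary in a journal article. The paired data will give each method's mean, the cross-table behind kappa shows direction in its margins, and a fuller plan could name a paired CI. Part of this stands: nothing stops the trial from answering the question with the data it collects. But the article did not leave the statistics open. It named them, and they do not fit its own first question. An analysis plan that followed the article faithfully would carry the mismatch forward.

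Three stronger readings are tempting, and the documents do not support them:

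- **That the coefficients carry no information on size.** This is exact only for correlation and consistency ICC. Absolute-agreement ICC and kappa do respond to the size of a systematic difference, though they mix it with random error.
- **That the ICC is computed on grouped data.** The closing phrase about groups may apply to kappa alone, which needs categories.
- **That app totals over three months are set against a single 30-day TLFB, so that falling consumption makes the app look higher.** The TLFB is a "structured interview for assessment of alcohol consumption during the last 30 days", but the article does not say which app days enter the comparison. It records the TLFB at every treatment session as well as at baseline, 3 and 6 months. It gives the follow-up AUDIT a 3-month reference period, and the app record can be viewed by day, week or month. A mismatch of windows is possible but not shown.

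**Conclusion.** The point holds in this form: no validation statistic named in the article gives the direction of the app-versus-TLFB difference, and the analyses of the trial outcomes do not supply it. The named analyses therefore leave the first research question unanswered. The loss of direction follows from the symmetry of the coefficients and rests on no assumed values. The figures (0.791 against 0.790 for ICC, 0.378 against 0.379 for kappa, at shifts of −4 and +4) are illustrations under assumed distributions. The near-equality for kappa also depends on cut-points that lie symmetrically about the mean. With other cut-points the two falls could differ, but kappa would still carry no sign.

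The consequence is confined to the validation part of the study. The primary and secondary RCT outcomes and their analysis are not affected. The change should be made, but the trial does not depend on it.

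**What to change.** In the Validation study section, add a main analysis for the first research question: the within-person difference (or ratio), Glasklart minus TLFB, in ungrouped standard drinks. Take both over the same calendar days, namely the TLFB window, using an interview whose window lies after the app was installed. Matching the days is a condition of this added analysis. Report the mean difference with its 95% CI and the limits of agreement, and answer the question from that CI. State in advance how a day without an app entry is read, since this can move the difference in either direction.

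Keep correlation, ICC and kappa as supporting results. State the form of the ICC, the weighting of kappa, and which of the two uses grouped values.

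iBAC readings are blood alcohol levels, not drinks. Make a signed comparison for iBAC only on a quantity that both methods can express in a common unit, and define that quantity beforehand. Otherwise limit any conclusion about higher estimates to Glasklart.

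The cost is a few sentences of analysis text and a date filter on app data already stored. No new data collection is needed.
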